## Abstract

**Background:**

Childhood obesity is a lifestyle-oriented disorder, which may lead to many comorbidities such as hypertension, coronary diseases, increased incidence of diabetes, and metabolic syndromes. Lack of diet control and increased screen time specifically after the COVID-19 pandemic among children and adolescents are the major reasons for this rising global concern. Despite various campaigns being carried out to lessen the rising rates of childhood obesity, the objectives have not yet been achieved. Ayurveda offers a multidimensional modality in managing children with overweight. The purpose of this study is to evaluate the combined efficacy of Ayurvedic medicine administration, diet restriction, and Sun Salutation. Navak Guggulu is a herbo-mineral compound already proven for its antiobesity action. Vachaharidradi Gana mentioned in Ayurvedic classics is a group of herbs, which are Kaphamedohara and Karshana. Ayurveda also emphasizes the importance of diet and physical activities for the treatment of obesity. The interventions together may help in promoting a healthy weight, improving metabolism, and reducing fat accumulation. So, in this study, the efficacy of Vachaharidradi Gana Vati will be compared with Navak Guggulu to treat children with overweight in addition to diet restrictions and Sun Salutation.

**Objective:**

The aim of the study is to evaluate the efficacy of Navak Guggulu versus Vachaharidradi Gana Vati along with diet restriction and Sun Salutation in overweight (Sthaulya) children.

**Methods:**

A double-blind randomized interventional study will be conducted on selected children with overweight in the age group of 10 to 16 years. They will be equally distributed into 2 groups. The control group will be given Navak Guggulu, and the trial group will be given Vachaharidradi Gana Vati for 90 days. Both groups will be advised of diet restrictions and the daily performance of the Sun Salutation. The study duration is 180 days, with assessment at baseline, followed by every 15 days up to 90 days, and at the end point, that is, after 180 days. Appropriate statistical techniques, such as analysis of covariance paired 2-tailed *t* test, Wilcoxon signed rank test, Mann-Whitney *U* test, and multivariate regression analysis, will be used to evaluate the efficacy of the interventions.

**Results:**

The study got underway in April 2024. Since participants may begin at any time, our goal is for everyone to be finished by May 2025.

**Conclusions:**

This research will be useful to provide new insight into the effectiveness of the Ayurveda pharmacological approach in treating obesity in children. The results will guide evidence-based multimodality in treatments aimed at changing lifestyle behaviors in children with obesity, thus reducing social stigmatization in them.

**Trial Registration:**

Clinical Trial Registry of India CTRI/2023/03/051135; https://ctri.nic.in/Clinicaltrials/pmaindet2.php?EncHid=NzgzNzE=&Enc=&userName=

**International Registered Report Identifier (IRRID):**

DERR1-10.2196/58838

## Introduction

### Background

India is going through a socioeconomic, nutritional, cultural, and health transformation. In recent years, the country has been witnessing an increase in the overnutrition rates in children. It shows the emergence of the dual nutrition burden in India, namely, overnutrition and undernutrition. Overnutrition among children manifests in overweight or obesity. Children from affluent urban families are more prone to obesity; however, recent data indicate a significant rise in obesity rates among low-income groups in both rural and urban areas. Globalization has introduced multinational fast-food chains across India, leading to a shift from traditional to modern eating habits. This transition has resulted in increased consumption of processed, high-calorie, ready-made foods, particularly among children. Such foods, rich in sugars and salts, have significantly influenced dietary preferences [1-4].

According to the International Obesity Task Force categorization in 2013, the overall prevalence of overweight and obesity was 18.2% and 23.9%, respectively, as per World Health Organization (WHO) standards [5]. As per computation by Lobstein and Jackson-Leach [6], we expect the number of children with obesity in India to reach 17 million by the end of 2025. In a systematic review, the pooled data from the states of India after 2010, the combined prevalence of childhood overweight and obesity was predicted to be 19.3% [7]. The COVID-19 pandemic situation further added a load to it [8]. During the lockdown, web-based schooling forced children to stay indoors, which reduced their physical activity and increased their screen time, leading to prolonged sitting with increased screen time. Excessive screen time reduces physical activity, which results in fat deposition at an early age [9].

Overweight or obesity is characterized by increased weight, increased weight for height, and raised BMI [10]. Recently, new Indian standards have been notified, and new 5- to 17-year charts of BMI for boys and girls have been published by the Indian Academy of Pediatrics. According to that, the BMI cutoffs for overweight and obesity in children are defined at 23 and 27 kg/m^2^, respectively (Indian Academy of Pediatrics 2015) [11]. Obesity is a risk factor for numerous noncommunicable diseases, including type 2 diabetes mellitus, asthma, joint pain, and multiple health conditions [12-16]. It frequently carries a high risk of early mortality and significant disability [17]. Children with overweight are more likely to experience cognitive developmental issues and are more likely to become adults with obesity. Obesity prevention should begin in childhood. According to the WHO expert constitution, on average, obesity reduces life expectancy by 6-7 years in adults [18-20].

Despite various campaigns being carried out to lessen the rising rates of childhood obesity, the objectives have not been achieved. The main causes include lack of awareness, poor adherence to balanced diet guidelines, and the absence of comprehensive policies to address this hidden epidemic [21]. It has become the need of the hour to recognize children with overweight and treat them as early as possible.

According to Ayurvedic classics, Sthaulya can be correlated with overweight or obesity. It is a Santarpanajanya Vyadhi [22], which means the disease caused due to excessive intake of food and decreased physical activities. In Ayurveda, the management of Santarpanajanya Vyadhi is a multidimensional modality. It includes medicine administration, Nidanaparivarjana [23] (avoidance of causative factors), diet control, and Vyayama (physical exercise). Ayurveda offers various medicines for the treatment of Sthaulya. Navak Guggulu is a well-known polyherbal compound containing guggulu (*Commiphora mukul* Linn) as the main ingredient. This compound is reported for its antiobesity action [24-27]. It has also been studied in the management of hyperlipidemia [28]. Though it is a proven drug, the availability of pure guggulu is a difficult task day by day. There is a scarcity of pure guggulu, and it is a tedious job to purify guggulu for oral administration, as the available guggulu contains many impurities.

Vachaharidradi Gana mentioned in Ayurvedic classics is a group of herbal medicines that have properties of Kaphamedohara (alleviating Kapha and reducing fats) and Karshana (therapeutic scraping). These are the characteristics of the medications that are recommended in the management of Santarpanajanya Vyadhi like overweight and obesity to improve fat metabolism. As a result, it should aid in maintaining weight and BMI. Further, the contents of Vachaharidradi Gana are easily available and cost-effective as well.

Diet control is as important as medicines in the management of Sthaulya. Bad eating habits are the main cause of obesity among children [29]. Eating in front of the television screen, drinking sugar-sweetened beverages, eating junk foods and packaged foods, and eating without hunger are the factors responsible for gaining excessive weight. Ayurveda has also emphasized the importance of diet in one’s health by phrasing it as “Mahabheshaja,” which means the most important medicine [30]. Therefore, strict diet control must be advocated for the management of children with overweight.

Physical activity is also important for preventing and managing obesity. Lack of exercise and obesity go hand in hand. Increasing physical activity in children is a nonrestrictive approach to obesity management, which is the discretionary component of energy expenditure [31,32]. Suryanamaskara (Sun Salutation) mentioned by Sayanacharya [33] is an ancient, Vedic, and sacred yogic technique that evolved in India for expressing gratitude to the Lord Sun. It is a series of asanas (postures). It helps in the activation of fat metabolism by rigorous movements and ultimately helps in the reduction of fat, thus beneficial in BMI reduction [34]. It also helps in psychological well-being [35], which will lead to a decrease in screen time.

If children with overweight are educated enough about diet restriction and performing Suryanamaskara along with Ayurvedic remedies, it will be beneficial to them to lead a healthy and happy life.

### Objectives

The aim of the study is to evaluate the equivalent efficacy of Navak Guggulu versus Vachaharidradi Gana Vati along with diet restriction and Suryanamaskara in children with Sthaulya (Overweight).

#### Primary Objectives

The primary objectives are (1) to evaluate the clinical efficacy of Navak Guggulu along with diet restrictions and Suryanamaskara in children with Sthaulya (overweight) on BMI and other parameters, (2) to evaluate the clinical efficacy of Vachaharidradi Gana Vati along with diet restrictions and Suryanamaskara in children with Sthaulya (overweight) on BMI and other parameters, and (3) to compare the efficacy of Navak Guggulu and Vachaharidradi Gana Vati along with diet restrictions and Suryanamaskara as adjuvant therapies in children with Sthaulya (overweight) on BMI and other parameters.

#### Secondary Objectives

The secondary objectives are (1) to evaluate the residual efficacy of Navak Guggulu versus Vachaharidradi Gana Vati in children with Sthaulya (overweight) after discontinuation of treatment after 180 days as well; (2) to study the effect of desha, kala, and prakruti on the children with overweight; and (3) to study the adverse effects of Vachaharidradi Gana Vati if any.

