### Ethical Considerations

The Mahatma Gandhi Ayurved College Hospital and Research Centre’s Institutional Ethics Committee approved this study (registration: MGACHRC/IEC/July-2022/521), and it was also registered with the Clinical Trial Registry of India (CTRI/2023/03/051135). The same ethical committee also approved the addition of the site at CSMSS Ayurved College, Chhatrapati Sambhajinagar. After receiving a No Objection Certificate from the institutional ethical committee of the CSMSS Ayurved College (AMCS/1407/2023), the participant recruitment at both sites will be initiated. The institutional ethical committee will decide on the end point and oversee the trial as it progresses. The researchers will assess any adverse events and will report to the ethics committee. Consent from parents and assent from patients (older than 12 years) will be obtained before conducting the trial in the local language while explaining every aspect of the study. Every participant will get information regarding the study’s design and objectives, data confidentiality, and the freedom to withdraw from the study at any moment without giving a reason. The informed consent form includes a patient information sheet (part 1) and a certificate of consent (part 2). Secondary analysis will be covered without additional consent. Data will be anonymized, and the personal information of the participants will be kept confidential before, during, and after the trial. Physical data will be stored in a protected storage facility, with access available only to the researchers. Computerized data will be held in a password-protected computer. Data access will be restricted to members of the research team only. During data analysis, measures will be taken to protect participants’ privacy. Participation in the study is completely voluntary; hence, no incentive will be provided to the participants. During the treatment period, if the patients’ condition worsens, the case will be excluded and will receive conventional treatment and care until the symptoms subside, free of charge. The ethics committee will be informed of the patient’s condition. The therapy will be discontinued, and the child will be withdrawn from the study if any other illness arises during the treatment period that could influence study outcomes. Similarly, if a participant experiences personal issues that prevent continuation of therapy and are likely to affect the study results, they will also be withdrawn. If the patient misses any of the periodic follow-ups during the intervention, they will be excluded from the study.

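### The safety objective is worded for the trial drug alone, and the exclusion rules do not say whether an excluded child's adverse events stay in the safety result

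*Protocol article*

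**What the plan says.** Everything here is in the protocol article.

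- **Secondary Objectives.** The third objective is "to study the adverse effects of Vachaharidradi Gana Vati if any". The first, in the same sentence, is comparative: "to evaluate the residual efficacy of Navak Guggulu versus Vachaharidradi Gana Vati". The third primary objective also compares the two drugs.
- **Secondary Outcome and Statistical Analysis.** The listed secondary outcomes are anthropometry, lipid profile and graded signs and symptoms. Adverse events are not among them. The analysis section describes within-group and between-group efficacy and mentions no safety comparison.
- **Ethical Considerations, adverse events.** "The researchers will assess any adverse events and will report to the ethics committee". Neither arm is singled out.
- **Ethical Considerations, exclusion and withdrawal.** For a child who gets worse while on treatment, "the case will be excluded and will receive conventional treatment and care until the symptoms subside, free of charge", and "The ethics committee will be informed of the patient’s condition". Also, "the child will be withdrawn from the study if any other illness arises during the treatment period that could influence study outcomes", and "If the patient misses any of the periodic follow-ups during the intervention, they will be excluded from the study".
- **Study Design and Table 1.** The trial is double-blind with an active control and 44 children per arm. Both arms receive the diet restrictions and daily Suryanamaskara.

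**The concern.** Two features of the text bear on the harm result.

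First, an analysis that follows the objective literally would list events for Vachaharidradi Gana Vati only. Both arms share a restricted diet and a daily exercise routine, and both will have ordinary childhood illness over 90 days. Complaints from those sources appear in a one-arm listing alongside any drug effect. The randomised control arm is what allows them to be told apart.

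Second, the rules for exclusion and withdrawal are linked to events that may themselves be harms or follow from them. A child may worsen, develop another illness, or stop attending because a tablet disagrees with them. The text does not separate stopping treatment, leaving follow-up and leaving the analysis. It also does not say that events already recorded for such a child are kept.

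The article presents the new tablet as a more available and affordable alternative to the control drug for children, and looks ahead to its commercialisation. The harm count is therefore likely to be relied on.

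**Working it through.** The plan states no safety figure, so there is nothing to reproduce. The check compares the sections first and then illustrates the size.

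**1. Objective against design.** Secondary Objectives limits safety to the trial drug. Ethical Considerations covers any adverse event without naming an arm. Study Design makes the trial double-blind, and Allocation Implementation keeps the treatment envelopes sealed until the last visit of the last child. Staff who do not know the allocation cannot collect events in one arm only, so control-arm events should exist. What is missing is a stated intention to compare them.

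**2. Objective against outcomes.** Adverse effects are a secondary objective, but Secondary Outcome contains no matching outcome and Statistical Analysis speaks only of efficacy.

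**3. Exclusion against reporting.** The three rules in Ethical Considerations act during the intervention and apply to both arms. The ethics committee is told of children who worsen. Nothing is said about whether an excluded or withdrawn child stays in the numerator or denominator of the trial's own safety result.

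**4. Size of a possible loss (event counts are assumed).** Input from the plan: 44 children per arm. Intervals are exact 95% (Clopper-Pearson): lower limit is the 0.025 quantile of Beta(x, n−x+1), upper limit the 0.975 quantile of Beta(x+1, n−x). Suppose 4 children in the trial arm are harmed.

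- All four counted: 4/44 = 9.1% (2.5% to 21.7%).
- Two dropped from numerator and denominator: 2/42 = 4.8% (0.6% to 16.2%).
- All four dropped: 0/40 = 0%, upper limit 1 − 0.025^(1/40) = 8.8%.

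**5. What the comparator adds (rates are assumed).** Suppose 4 of 44 children in each arm have complaints caused by diet or exercise. A one-arm listing shows 9.1% with nothing to set against it. The two-arm difference is 0, with 95% half-width 1.96 × √(2 × 0.0909 × 0.9091/44) = 0.120, or 12 percentage points.

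**6. Precision of the comparison.** With a common rate p, the half-width is 1.96 × √(2p(1−p)/44):

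- p = 5%: 9.1 points
- p = 10%: 12.5 points
- p = 20%: 16.7 points

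Power by the normal approximation at two-sided 5% is Φ[(Δ − 1.96·SE₀)/SE₁], where SE₀ uses the pooled rate and SE₁ the separate rates:

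- 5% v 15%: 34%
- 5% v 20%: 57%
- 5% v 25%: 76%

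The comparison is possible but imprecise.

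**The case against.** The strongest reply is that the comparator is not missing. Events are to be assessed without restriction to an arm, and blinding makes one-arm collection impracticable. This stands. A reader might infer from the objective that the harm result will have no randomised control, but the article does not support that. It lacks only a planned comparison.

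Next, the exclusion sentence concerns care and is followed by notification of the ethics committee. Nothing in it says that recorded events are deleted, and worsening may refer to the overweight condition itself rather than a drug effect. This also stands. A reader might infer that harm cases will be removed from the reported data, but exclusion is left undefined, so loss is a risk and not a stated outcome. Notifying the committee gives oversight, yet it does not by itself keep those children in the trial's result.

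Third, an article may leave the safety population and tables to the full protocol or SAP. That is fair for analysis detail. It does not cover an objective that is itself worded for one arm, or exclusion rules that are stated without their consequence for reporting. An analysis plan that implemented this text faithfully would carry both forward.

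Fourth, the control drug is presented as established, so it is natural to name the new one. That explains the wording, but diet, exercise and illness are common to both arms and still have to be separated from the new drug's effects.

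Finally, one might measure the problem by the upper confidence limit after zero events. That limit depends only on the number of children and would be the same after rewording, so it does not measure this defect.

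**Conclusion.** The point holds in a limited form. As written, no between-arm safety comparison is planned, although the data for one should be collected. The effect of exclusion or withdrawal on the safety result is unspecified, so harm cases could drop out of it.

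The size cannot be fixed from the article, which gives no expected event rates. In the assumed example, losing four harmed children from one arm moves the estimate from 9.1% to 0%. The actual effect depends on how many harmed children meet an exclusion or withdrawal rule and on how exclusion is applied, and it could be nil if all recorded events are kept. The direction of any error in a between-arm contrast is not determined, because the rules apply to both arms.

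This should be corrected because the change is small. It does not show that the planned safety data are unusable, and it passes no judgement on how a child who worsens should be managed.

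**What to change.** - Reword the third secondary objective as a comparison of adverse events between Vachaharidradi Gana Vati and Navak Guggulu.
- Add adverse events to the secondary outcomes.
- Report them by randomised arm, with the number of children affected and a risk difference with its confidence interval, in all children who took at least one dose, including those later excluded or withdrawn.
- State in Ethical Considerations that exclusion or withdrawal does not remove a child's recorded events from the safety result. Leave the clinical handling of worsening as it is.

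The cost is a few sentences and one extra table, largely from events the researchers already have to assess. At 44 per arm the interval for the difference will be wide (about ±9 to ±17 points at event rates of 5% to 20%). The result should be presented as an estimate with its uncertainty, and the absence of a significant difference should not be read as equal safety.

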### Hypotheses

The hypotheses are as follows:

H0 null hypothesis: Vachaharidradi Gana Vati and Navak Guggulu along with diet restrictions and Suryanamaskara are not equivalent in efficacy in reducing the BMI in children.H1 alternate hypothesis: The efficacy of Vachaharidradi Gana Vati is equal to Navak Guggulu along with diet restrictions and Suryanamaskara in reducing the BMI in children.

## Methods

### Study Design

A randomized, standard-controlled, double-blind equivalence clinical trial will be performed. The study flow is depicted in Figure 1. The study participants required for the trial include children with overweight aged between 10 and 16 years of age will be selected from the Outpatient Department and Inpatient Department of the Department of Kaumarbhritya, Mahatma Gandhi Ayurveda College Hospital and Research Centre, Salod (H), and Chhatrapati Shahu Maharaj Shikshan Sanstha’s (CSMSS) Ayurved College and Hospital, Chhatrapati Sambhajinagar, based on the inclusion criteria.

Overweight (Sthaulya) children will be diagnosed as having a BMI greater than or equal to 23 and less than 27 kg/m^2^ [11]. Screening will include hemoglobin percentage, thyroid-stimulating hormone, and random blood sugar. A total of 88 diagnosed children with overweight will be selected after obtaining written informed consent from their guardians. Participants will be randomly divided into 2 groups by block randomization using a computerized random number generator or statistical software. Group A (control group) will receive Navak Guggulu, while group B (trial group) will receive Vachaharidradi Gana Vati orally (Table 1). Medications will be dispensed in opaque containers following the sequentially numbered, opaque, sealed envelope (SNOSE) technique to maintain allocation concealment. Both groups will receive counseling to perform 12 Suryanamaskara (Sun Salutation) per day and adhere to the dietary restrictions. Guardians will be educated and advised to support their children’s consistent participation in the interventions. All the baseline parameters will be recorded at the study’s initiation. The treatment duration will be 90 days, with follow-up assessments on the 15th, 30th, 45th, 60th, 75th, and 90th day to monitor progress and ensure adherence. Lipid profile will be assessed before treatment and on the 90th day of intervention to evaluate the efficacy of the interventions. An additional follow-up will occur on the 180th day to determine whether the intervention’s possible effects are lasting.

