### Inclusion Criteria

The inclusion criteria are as follows: participants irrespective of gender, religion, and socioeconomic status, age group between 10 and 16 years with signs and symptoms of overweight (Sthaulya) due to exogenous causes, participants with BMI ≥23 and <27 kg/m^2^, and parents who are willing to provide written informed consent for their children to be included in the study.

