### Outcomes

#### Primary Outcome—BMI

BMI will be calculated as the ratio of body weight to the square of height (kg/m^2^). Indian Academy of Pediatrics 2015 charts will be used to categorize weight as normal, overweight, and obese.

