### Statistical Analysis

The statistical analysis will be performed at the end of the study. It will involve various tests to evaluate both within-group and between-group efficacy of Navak Guggulu and Vachaharidradi Gana Vati in managing Sthaulya (overweight) among children. For normally distributed continuous variables like BMI, WHR, and skinfold thickness, paired 2-tailed *t* tests will be used to evaluate the efficacy of each intervention within the same group (pre- and posttreatment comparisons).

For nonnormally distributed data, the Wilcoxon signed rank test will be used. For normally distributed data, independent 2-tailed *t* tests will be used for between-group comparisons of mean changes; for nonnormal data, the Mann-Whitney *U* test will be used.

To ensure valid comparisons, the analysis of covariance will be used to account for any potential baseline variations between groups. To evaluate residual efficacy after treatment discontinuation at 180 days, repeated measures ANOVA will analyze longitudinal changes in outcomes, while mixed-effects models will handle missing data or variability across time points. For stratified analysis based on Desha (geography), Kala (season), and Prakruti (body constitution), multivariate regression analysis will identify predictors of treatment efficacy, and interaction analysis will explore the influence of these factors. A statistician consultation will be considered for the selection of the proper statistical method.

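### Within-arm statements on efficacy, and on whether effects last to day 180, rest on raw BMI in growing children and so mix growth with treatment effect; the randomised comparison is not biased by this

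*Protocol article*

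**What the plan says.** All references are to the protocol article.

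- **Outcome scale.** Primary Outcome—BMI: "BMI will be calculated as the ratio of body weight to the square of height (kg/m^2"). The same section gives the charts a sorting role only: "Indian Academy of Pediatrics 2015 charts will be used to categorize weight as normal, overweight, and obese".
- **Charts and cut-offs.** Background reports that "new 5- to 17-year charts of BMI for boys and girls have been published by the Indian Academy of Pediatrics", and that "the BMI cutoffs for overweight and obesity in children are defined at 23 and 27 kg/m^2^, respectively".
- **Population.** Inclusion Criteria: "age group between 10 and 16 years with signs and symptoms of overweight (Sthaulya) due to exogenous causes".
- **Schedule.** Study Design: "The treatment duration will be 90 days, with follow-up assessments on the 15th, 30th, 45th, 60th, 75th, and 90th day". Then: "An additional follow-up will occur on the 180th day to determine whether the" possible effects endure.
- **Arms.** Table 1 lists two active arms of 44 each. Both receive the same diet and Sun Salutation advice. There is no untreated or lifestyle-only arm.
- **Objectives.** Primary objectives 1 and 2 evaluate each regimen separately on BMI; objective 3 compares them. The first secondary objective is residual efficacy of one drug against the other.
- **Analysis.** Statistical Analysis plans paired t tests within each arm, independent t tests on mean changes between arms, and ANCOVA for baseline differences with no covariates listed. For residual efficacy at day 180, "repeated measures ANOVA will analyze longitudinal changes in outcomes", with mixed-effects models for missing data.

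**The concern.** Charts specific to age and sex are of use because expected BMI depends on both. A child who keeps the same chart position may therefore change in raw BMI simply by growing. In a before-and-after comparison within one arm, that change is added to whatever the regimen does. If expected BMI rises with age, growth hides part of a real reduction by day 90. Between day 90 and day 180 it looks like a fading effect.

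This affects the answers to primary objectives 1 and 2, and any statement that a regimen's effect has lasted or been lost. The between-arm difference does not fill that gap alone. A difference near zero at day 180 fits both effects persisting and both vanishing, so authors will be drawn to the change over time within each arm, which is where growth enters.

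**Working it through.** **Inputs from the protocol.** Planning SD 0.86 and difference 0.57 kg/m^2 (Participants); 39 per arm before dropout; 90 days on treatment and 90 days off.

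**The plan's own figure.** The protocol gives no figure for growth or persistence. Its only relevant calculation is the sample size. The printed expression gives 2 × (1.96 + 0.84)^2 × 0.86^2 / 0.57^2 = 35.69, so 36 per arm rather than the stated 39. The stated 39 is obtained with z values of 1.645 and 1.282: 2 × (1.645 + 1.282)^2 × 0.86^2 / 0.57^2 ≈ 38.99. Nothing below depends on which is used; I take 39.

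**Assumption.** Expected BMI rises by 0.3 to 1.0 kg/m^2 per year at these ages.

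**Within-arm drift** = annual rise × days / 365.25.

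| Assumed rise per year | 90 days | 180 days |
|---|---|---|
| 0.3 | 0.074 (13% of 0.57) | 0.148 (26%) |
| 0.5 | 0.123 (22%) | 0.246 (43%) |
| 0.7 | 0.172 (30%) | 0.345 (61%) |
| 1.0 | 0.246 (43%) | 0.493 (86%) |

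The 90-day column applies to the baseline to day 90 tests and to the off-treatment interval. The 180-day column applies to baseline to day 180. The percentages only give scale, because 0.57 is a between-arm planning difference.

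**Against within-arm precision.** If 0.86 is also the SD of change within an arm (a further assumption), the standard error of a mean change is 0.86 / √39 = 0.138. Drift is then 0.54 to 1.79 standard errors over 90 days and 1.07 to 3.58 over 180 days. At the upper end, growth alone could decide a paired test.

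**Between-arm contrast.** Growth common to both randomised arms contributes zero in expectation. For chance imbalance, assume growth rates vary between children with an SD of 0.2 to 0.5 kg/m^2 per year:

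- Added standard error at 180 days = SD × (180/365.25) × √(2/39) = 0.022 to 0.056.
- Planning standard error = 0.86 × √(2/39) = 0.195.
- Combined at the upper end = √(0.195^2 + 0.056^2) = 0.203, about 4% larger. At the lower end the increase is below 1%.

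Both terms carry the same √(2/n), so the ratio does not change with the sample size.

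**The case against.** The strongest reply is that this is a randomised comparison of two drugs. The hypotheses are between drugs, and so is the residual-efficacy objective. Growth cancels there in expectation and the precision cost is under 5%. That stands, and it limits the point to within-arm statements. A reader might infer that the whole day-180 answer is distorted; the documents do not support that.

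Three other stronger readings also fail.

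- **Ageing into a better category.** A reader might argue that a child with unchanged BMI could improve in weight category by ageing past a rising cut-off. The protocol states only fixed values, 23 and 27 kg/m^2, in Background and again for diagnosis and eligibility. Under those, an unchanged BMI stays in its category.
- **Age and sex left out of the model.** The ANCOVA sentence lists no covariates and excludes none. A covariate list is commonly left to the analysis plan, so its absence is not an error. Naming age and sex is an improvement, not a correction.
- **A known size of distortion.** The protocol has no growth rate, so the drift is wholly assumed. For fading after treatment stops, the relevant interval is 90 days, not 180.

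Two further limits stand. The protocol does not name which outcomes are read at day 180; that BMI is among them is inferred from its primary status and from the reference to outcomes in the repeated measures analysis. And standardising for age and sex removes average growth only. Regression to the mean (entry is selected on BMI), season, and continuing diet and exercise would still affect a within-arm change.

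**Conclusion.** The concern holds for within-arm statements: primary objectives 1 and 2 with their paired tests, and the question of whether each regimen's effect lasts to day 180. As planned, these rest on raw BMI change in children aged 10 to 16 with no untreated arm, so growth cannot be told apart from a treatment effect or its loss.

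At an assumed 0.3 to 1.0 kg/m^2 per year, the drift is roughly 0.07 to 0.25 kg/m^2 over the off-treatment interval and 0.15 to 0.49 over the full study. The direction, a maintained effect looking partly lost, depends on expected BMI rising with age.

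The between-arm contrasts at days 90 and 180 are not biased. This is a cheap improvement in what the trial can say about persistence, not a flaw in the primary comparison.

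**What to change.** 1. Keep raw BMI as the primary outcome.
2. Fit the between-arm model with baseline BMI, age and sex as fixed covariates, whatever imbalance is observed.
3. Analyse BMI-for-age (z-score or centile for age and sex at the visit, from the charts already named) at baseline, day 90 and day 180, alongside raw BMI.
4. Base persistence statements on the between-arm difference and the BMI-for-age change, not on raw within-arm BMI change.
5. State in the report that within-arm changes remain uncontrolled for other influences, such as regression to the mean.

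**Cost.** A little analysis work and two degrees of freedom for age and sex. Height and weight are already measured, age is an eligibility criterion, and sex is needed to use the charts. No extra visit, measurement or participant is required.

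**What it does not do.** It removes average growth from the within-arm reading but does not turn that reading into a controlled comparison.
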